Using the practice schedule concept of motor learning to PBBT is a relatively new approach [8]. There are two types of practice schedules:constant and variable. Constant practice involves repeatedly practicing a single skill. In contrast, variable practice exposes the learner to a variety of related skills [9]. Performing variable skills within a single practice session creates contextual interference (CI), a phenomenon that enhances long-term learning by requiring frequent shifts between task variations [10]. Variable practice is broadly categorized into blocked or random schedules [11]. Blocked practice, associated with low CI, involves repeated performing of one task before moving to another, facilitating skill acquisition and performance during training [11]. Random practice, associated with high CI, refers to practice task variations in the same session in a pseudo-random order [11]. Although acquisition may be slower, random practice leads to better skill retention and transfer to new situations [12].

Given the crucial role of reactive responses in preventing falls, which are often sudden and occur in any direction [13], it is important to investigate how different practice schedules affect the ability of individuals with DPN to react to balance perturbations. In addition, In individuals with DPN, compensating for sensory loss increases cognitive demand, causing balance impairments during dual-tasking [6]. Since reactive balance requires attention, dual tasks may further disrupt postural control strategies in these individuals [14]. Therefore, assessing the generalizability of improvements in reactive balance control during single-task to dual-tasks may be useful for enhancing dual-task interference on reactive balance performance in individuals with DPN.

To the best of our knowledge, no study has yet investigated the effects of different practice schedules of PBBT on reactive balance control in individuals with DPN. Therefore, this study aims to compare the effects of blocked and random practice of PBBT on the acquisition, retention, and generalizability of acquired reactive balance skills in individuals with DPN. Our findings would be helpful for the development of preventive and therapeutic strategies to reduce the risk of falls and improve reactive balance control in individuals with DPN.

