### Methods of measurement

Participants will be evaluated at a pre-test (T1), post-test (T2), and retention test (T3) using the same protocol. In these tests, each participant will receive two trials of perturbations with each of the three difficulty levels and the anterior direction with a serial sequence (totaling six trials). Serial sequence refers to the sequence or arrangement of different skills, or variations of a skill, in a specific order, one after another in a predictable manner. The post-test is applied five minutes after PBBT.

The retention test will be applied at the beginning of the second session. After a five-minute rest, patients will be tested in three different transfer tasks.

Transfer tasks will be assessed as follows:

Cognitive dual-tasking: counting backward by three from a random number selected between 100 and 200 by the outcome assessor during perturbations. Participants will be asked to maintain balance while they attempt to perform the consecutive mental subtractions task as quickly and as accurately as possible, speaking aloud the result. During this cognitive transfer task, the high level of difficulty perturbation will be applied in the anterior direction, with two trials.

Different mode of perturbation: In this test, the perturbation will be in the anterior (dorsiflexion) direction with a rotational mode, with two trials.

Choice Stepping Reaction Time (CSRT) Test: for assessing the transferability of improvements obtained in the reactive balance responses to the balance responses against internal perturbations, the CSRT test will be used. In this test, patients will stand on a long force plate of the Neurocom device with their feet hip-width apart, and while looking at the screen in front of them, colored boxes are randomly displayed on the right or left side of the screen. Participants will be instructed to step as fast as possible with the respective leg and then return to the starting position. Each participant will perform 10 trials, which include five repetitions for each direction randomly [19]. A one-minute rest period will be allowed between transfer tests. In order to have a baseline in this study, all transfer tests will be assessed before training.

Reactive balance control is the main outcome in this study, which will be recorded with the Computerized Dynamic Posturography system in the standing position [20].

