### Statistics

All data will be analyzed using SPSS version 28. Baseline data and demographic characteristics will be described using descriptive statistics.

Data distribution normality will be confirmed using the Kolmogorov–Smirnov test. The main effects and interactions of group (blocked sequence, random sequence, and control), time (pre-test and post-test), and difficulty level (low, medium and high) on CoP variables will be compared using three-way repeated measures ANOVA. In addition, the main effects and interactions of groups, time (post-test and retention), and difficulty level (low, medium, and high) on CoP variables will be compared using three-way repeated measures ANOVA. Also, a one-Way ANOVA will be used to compare the means of CoP variables between the retention and transfer phases across three groups. Moreover, a two-way repeated measure ANOVA will be used to determine the main effects and interactions of group and time (pre-test, post-test, and transfer) on RT, MVT, and TRT variables of the CSRT test. A post-hoc Bonferroni test will be used for multiple comparisons.

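### The one-way ANOVA planned for the two CoP transfer tasks does not fit a within-patient phase comparison, and no reading of it is both faithful to the wording and a good test of generalizability

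*Protocol article*

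**What the plan says.** The Background gives the aim as to "compare the effects of blocked and random practice of PBBT on the acquisition, retention, and generalizability of acquired reactive balance skills". Generalizability is examined with three transfer tasks, described under Methods of measurement. In the second session the retention test comes first; then "After a five-minute rest, patients will be tested in three different transfer tasks".

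The tests that yield CoP data differ in content:

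- Retention: "each participant will receive two trials of perturbations with each of the three difficulty levels and the anterior direction with a serial sequence" (six trials).
- Dual-task transfer: "the high level of difficulty perturbation will be applied in the anterior direction, with two trials".
- Rotational transfer: "the perturbation will be in the anterior (dorsiflexion) direction with a rotational mode, with two trials".

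The third transfer task, Choice Stepping Reaction Time (CSRT), yields step times instead.

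The same section states: "In order to have a baseline in this study, all transfer tests will be assessed before training". Table 1 agrees, marking all three transfer tasks at both T1 and T3.

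For the CoP transfer data the Statistics section plans that "a one-Way ANOVA will be used to compare the means of CoP variables between the retention and transfer phases across three groups". For CSRT, by contrast, "a two-way repeated measure ANOVA will be used to determine the main effects and interactions of group and time (pre-test, post-test, and transfer"), applied to the step-time variables. Bonferroni post-hoc comparisons are planned.

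**The concern.** The CoP transfer sentence names two dimensions, phase and group, but a model with one between-patient factor. Every other inferential model in that paragraph is a repeated-measures ANOVA. The reader cannot tell what the single factor is, what the dependent variable is, or how two values from one patient are to be handled. Different answers give different error rates and address different questions.

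The contrast itself is a second problem. Retention and transfer differ in perturbation mode, difficulty mix and cognitive load, so the gap between them reflects the tasks as well as learning. The Background expects random practice to help both retention and transfer. A contrast between the two removes whatever they share.

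Third, the T1 dual-task and rotational scores are collected to serve as a baseline, yet no CoP analysis in the Statistics section uses them.

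At stake is the CoP part of one of the three stated aims.

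**Working it through.** **Inputs.** From the protocol: three groups of about 20, two phases per patient at T3, alpha 0.05, Bonferroni post-hoc tests. Not given, so assumed: the within-patient correlation r (0.3 to 0.8, with 0.6 as the working value) and a random-versus-blocked difference of 0.8 SD.

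**The plan's own figure.** The only stated size, about 20 per group at 80% power, concerns the T1-T2 change in anterior peak CoP velocity, not transfer. It cannot be reproduced, because no effect size or SD is given. Solved backwards for two groups of 20 (normal approximation), it corresponds to d = (1.960 + 0.842) × √(2/20) = 0.886.

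**Step 1. Type I error if phase enters a one-way ANOVA.**

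*Phases compared within one group as if independent.* The true variance of the mean difference is 2σ²(1−r)/n, but the test uses 2σ²/n. At r = 0.6 the statistic shrinks by √0.4 = 0.632, so the critical value of 2.024 (38 df) acts like 2.024/0.632 = 3.20, a tail probability of about 0.3%.

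*Both phases pooled, group as factor.* The variance of a group mean is inflated by 1 + r = 1.6. The critical F(2,117) of 3.07 acts like 3.07/1.6 = 1.92. Since P(F > x) = (1 + 2x/117)^(−58.5), the level is about 15%.

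Simulation (3 × 20 patients, no effect, 40,000 runs) agrees:

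| r | Phase within a group | Pooled, group as factor |
|---|---|---|
| 0.3 | 2.0% | 9.9% |
| 0.5 | 0.7% | 13.9% |
| 0.6 | 0.4% | 15.8% |
| 0.7 | 0.1% | 17.5% |
| 0.8 | 0.0% | 19.5% |

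A third layout, six group-by-phase cells as one factor, keeps an overall level of about 4.5 to 5.6% but gives no separate group-by-phase test.

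**Step 2. One-way ANOVA across groups on the retention-transfer difference.** There is one value per patient, so the level is right (about 5% at every r). But suppose random training adds δ to both scores relative to blocked. The random group's expected difference is (transfer + δ) − (retention + δ) = transfer − retention, and δ vanishes. With δ = 0.8 SD on both, the random-versus-blocked test on the difference rejects in about 5% of trials, which is the false-positive rate. The same test on the transfer score rejects in about 69%.

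**Step 3. One-way ANOVA across groups on the T3 transfer score.** The level is again about 5%. What it loses is precision. Adjusting for the T1 score of the same task multiplies residual variance by 1 − r², which is 1 − 0.36 = 0.64 at r = 0.6. The standardised difference becomes 0.8/√0.64 = 1.0. Power comes from the noncentral t with noncentrality d√(n/2) and 38 df:

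- Unadjusted score: 0.8 × √10 = 2.53. Power is 69% at alpha 0.05 and 52% at 0.05/3.
- T1-adjusted score: 1.0 × √10 = 3.16. Power is 87% at alpha 0.05 and 74% at 0.05/3.

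Over the assumed range of T1-T3 correlation, adjusted power is:

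| r | Alpha 0.05 | Bonferroni, 0.05/3 |
|---|---|---|
| 0.3 | 73% | 56% |
| 0.5 | 81% | 66% |
| 0.6 | 87% | 74% |
| 0.7 | 93% | 84% |
| 0.8 | 98% | 95% |

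**The case against.** The best defence is that the reference to three groups makes group the single factor. On that reading the analysis is a one-way ANOVA on the transfer score, or on the difference, followed by Bonferroni. Both hold their level, and the first is a legitimate randomised comparison of random with blocked training. This stands. A reader might infer that the plan cannot show which schedule transfers better, or that it carries one definite wrong error rate. The documents support neither: the first inference fails on the transfer-score reading, and the error rate moves in opposite directions depending on layout. The defence does not rescue the sentence, however. The transfer-score reading has to set aside the stated comparison between phases, and the difference reading does not measure transfer gain.

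A reader might also infer that transfer as a whole is mishandled. It is not. CSRT has a group-by-time repeated-measures ANOVA that includes the pre-test.

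Nor does leaving out the T1 scores bias anything. Groups are randomised, so an unadjusted T3 comparison is unbiased and the loss is one of efficiency. The protocol says that a baseline is collected; it does not promise adjustment.

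Finally, it is tempting to say that a group with better retention must look worse on transfer. That requires the difference reading and a larger gain on retention than on transfer. With equal gains the gap is unchanged.

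**Conclusion.** The concern holds for the dual-task and rotational CoP tests. Taken literally, the planned model has no place for the within-patient factor it is asked to compare. The readings that hold their level either lose any benefit shared by retention and transfer, or abandon the stated comparison and leave the T1 scores unused. Leaving the choice open also allows it to be made after the data are seen.

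The type I error figures and the power gain rest on assumed correlations and an assumed 0.8 SD difference, since the protocol gives neither. The direction of each result does not depend on the exact values; the size does. Where the planned Bonferroni correction is kept, 52% to 74% is the relevant power comparison.

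This should be fixed but does not undermine the trial. The acquisition, retention and CSRT analyses and the sample-size variable are untouched.

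**What to change.** Replace the one-way ANOVA sentence. For each CoP transfer task (dual-task, rotational) and each CoP variable, fit an ANCOVA of the T3 score with group as factor, the same task's T1 score as covariate, and gender as a factor because it is the stratification variable in the Random allocation section. Report random minus blocked, random minus control and blocked minus control with 95% confidence intervals and the Bonferroni adjustment already planned.

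If the cost of the dual task is also of interest, state it as a separate question. Compare the dual-task trials only with the single-task high-difficulty anterior trials of the retention test, within patient.

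The cost is a change of wording. The T1 transfer measurements are already scheduled, and SPSS fits the model. The Protocol validation section says that the outcome assessment phase has not been reached, so on the article's own account the change can be made and dated before outcome data exist.

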## Description of protocol

### Study design

This single-blind randomized controlled trial will be conducted at the Rehabilitation Research Center located at the School of Rehabilitation Sciences, Ahvaz Jundishapur University of Medical Sciences, Ahvaz, Iran.

This study consists of two sessions. The first session consists of three parts; (1) pre-intervention assessments, baseline measurements will be performed by completing the questionnaires then implementing the pre-test, (2) 15-20 minutes of 24 unexpected perturbations while standing, and (3) post-test assessments. For the patients, this session will be followed by the second session 24 hours later, which include the retention and transfer tests. An overview of the study timeline, enrollment, and time points of assessment is presented in (Table 1).

**Table 1 tbl0001:** Participant flow of enrolment, assessments and interventions.

	T0	T1	TT	T2	T3
Recruitment	+				
Interview (inclusion/exclusion)	+				
Assigning Consent form		+			
Randomization		+			
Questionnaires (MMSE; NDS; BDI-13; Mini-BEST)		+			
Assessment of reactive balance responses (balance reactions while standing in pre-test, post-test, and retention test)		+		+	+
Perturbation training intervention			+		
Transfer tests		+		+	+
Dual task test transfer (Concurrent mental arithmetic task)		+			+
Rotational mode transfer		+		+	+
Choice Stepping Reaction Time (CSRT) Test		+		+	+

T0, prior to study; T1, baseline (pre-intervention); TT, training time; T2, post-intervention test; T3, second session (one day post-intervention). Abbreviations: MMSE, Mini-Mental Scale Examination; NDS, Neuropathy Disability Score; BDI-13, Short Beck Depression Inventory; Mini-BEST, Mini Balance Evaluation Systems Test.

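### The CSRT analysis names no test of 24-hour transfer: its overall interaction cannot tell a T2-only from a T3-only effect, and the Bonferroni step is not tied to a time point

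*Protocol article*

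**What the plan says.** All places are in the protocol article.

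- **Role of the test.** Under Methods of measurement, the Choice Stepping Reaction Time (CSRT) test is used "for assessing the transferability of improvements obtained in the reactive balance responses to the balance responses against internal perturbations". The Abstract lists reaction time, movement time and total response time among the primary outcomes.
- **Timing.** Table 1 (Study design) marks the row "Choice Stepping Reaction Time (CSRT) Test" at T1, T2 and T3. For T2, Methods of measurement says: "The post-test is applied five minutes after PBBT". T3 is the second session, one day later.
- **Model.** Statistics gives CSRT a single two-way repeated-measures ANOVA on "group and time (pre-test, post-test, and transfer) on RT, MVT, and TRT variables of the CSRT test". The groups are those named earlier in that section: "group (blocked sequence, random sequence, and control". Since the other two levels are pre-test and post-test, the level called transfer must be T3.
- **Follow-up step.** The next sentence reads: "A post-hoc Bonferroni test will be used for multiple comparisons". It names no contrast, visit or family.
- **Contrast with the CoP analysis.** The centre-of-pressure variables get two separate models, one over "time (pre-test and post-test), and difficulty level (low, medium and high) on CoP variables" and one over "time (post-test and retention), and difficulty level (low, medium, and high) on CoP variables".

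**The concern.** The Background expects practice schedules to act differently over time: random practice may be slower to acquire yet better retained and transferred. The T2 and T3 results on CSRT therefore answer different questions. For CoP the plan separates the immediate change from what follows it; for CSRT it puts both follow-up visits into one time factor. The overall interaction then asks whether the groups differ in any pattern over three visits, and the group main effect averages over them. Neither is a statement about 24 hours.

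What is left is the post-hoc step. Depending on how it is run, it may isolate T3, isolate it without using the baseline value, or not isolate it at all. At stake is which result carries the 24-hour transfer statement for a listed primary outcome, and how much power that result has.

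**Working it through.** **Inputs from the article.** Three groups of about 20 (Sample size calculation), three CSRT visits (Table 1), alpha 0.05.

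**Assumed, because the article gives no effect size, SD or correlation for CSRT.** Unit SD at each visit; the same correlation rho between any two visits, 0.5 or 0.7; a shift of 0.8 SD at one follow-up visit only.

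**No figure of the plan to reproduce.** The stated sample size concerns CoP velocity from T1 to T2 and comes without its inputs. It does not bear on this point.

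**1. Degrees of freedom.** Interaction (3 − 1)(3 − 1) = 4; error (3 − 1)(60 − 3) = 114.

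**2. What the interaction responds to.** If one arm shifts by 0.8 SD at one visit, the interaction effects have sum of squares 0.8² × (2/3) × (2/3) = 0.284. The result is the same if two arms shift together. The noncentrality is 20 × 0.284 / (1 − rho):
- rho 0.5: 11.4, giving power of about 76%
- rho 0.7: 19.0, giving power of about 95%

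Nothing in the expression depends on whether the shifted visit is T2 or T3. Simulation of 20,000 trials per setting, with both training arms shifted, agrees: 76.4% (T2 only) and 75.8% (T3 only) at rho 0.5; 94.4% and 94.6% at rho 0.7. With no effect anywhere, the rate is about 5%.

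**3. How large a T3-only effect looks in each candidate comparison.** The effect is divided by the SD of the quantity compared:

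| Comparison | SD | Standardised effect, rho 0.5 / 0.7 |
|---|---|---|
| T3 unadjusted | 1 | 0.80 / 0.80 |
| T3 adjusted for T1 | √(1 − rho²) = 0.866 / 0.714 | 0.92 / 1.12 |
| T3 minus T1 | √(2(1 − rho)) = 1.00 / 0.775 | 0.80 / 1.03 |
| Mean of three visits | √((1 + 2rho)/3) = 0.816 / 0.894 | (0.8/3)/SD = 0.33 / 0.30 |

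The last row is the same for a T2-only effect.

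**4. Simulated rates of a significant result, 0.8 SD effect (rho 0.5 / 0.7 where two values are given).**

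| Procedure | T2 only (no 24-hour effect) | T3 only |
|---|---|---|
| Overall 4-df interaction | 76% / 94% | 76% / 95% |
| Interaction significant, then unadjusted Bonferroni between groups at T3 | about 4% | 58% / 67% |
| Bonferroni on group means averaged over time | 12–15% | about 14% |
| 2-df group test on T3 minus T1 | about 5% | 72% / 92% |
| T3 adjusted for T1, Bonferroni over three pairs | below 5% | about 80% / 93% |

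For T2-only effects of 0.5 to 1.0 SD, the second row's false T3 rate ranges from 2% to 4.5%.

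**The case against.** The strongest reply is the Bonferroni sentence. A significant interaction followed by group comparisons at each visit is a usual way to locate an effect, and it keeps false T3 findings at about 4%. That stands. A reader might infer that no planned test can isolate T3, or that a benefit present only minutes after training will be reported as 24-hour transfer. The article supports neither: the post-hoc step may be run at T3, and nothing says the overall p-value will be read as a T3 result.

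Nor are the 76% and 95% error rates. When groups differ at T2 only, a group-by-time interaction truly exists, and rejecting its absence is correct. A reader might also infer that the model could favour the wrong schedule. It could not by itself: an overall interaction has no direction, and a reversal between schedules from T2 to T3 is a pattern it can detect.

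It is also fair that CSRT at T2 is transfer of a kind, since Table 1 marks transfer tests at T2 too. The distinction is between immediate and 24-hour transfer.

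Last, a list of post-hoc contrasts is often left to the analysis plan, which is not shown. Silence on that list alone would be no finding. But the model is stated, and it treats CSRT differently from CoP. Even the most favourable reading of the post-hoc step makes no use of the T1 value within the T3 comparison, so the proposed change does more than write down a missing label.

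**Conclusion.** The point holds in a limited form. The stated CSRT interaction responds alike to a T2-only and a T3-only effect and cannot alone support a 24-hour transfer statement. The post-hoc step could supply that support if run between groups at T3, at a false-positive rate of about 4%, but the text does not tie it to T3. Run on means averaged over visits, it would not separate T2 from T3 (about 14% significant in either case).

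The main measurable loss is power for a T3-only effect: 58% to 67% on the favourable reading against about 80% to 93% with adjustment for T1. These figures assume a 0.8 SD effect, 20 per group and equal between-visit correlations of 0.5 to 0.7, none of which the article gives for CSRT. The near-equality of T2-only and T3-only rates rests on the equal correlations; the absolute rates move with the effect size.

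**What to change.** In Statistics, for each of RT, MVT and TRT:

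- name the group comparison at T3 adjusted for the T1 value, with Bonferroni over the three group pairs, as the test of 24-hour transfer;
- report the group comparison at T2 adjusted for T1 separately, as immediate transfer;
- state that the 24-hour conclusion does not rest on the overall interaction or the group main effect.

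The change is to analysis wording only and uses data already planned at T1, T2 and T3. The Protocol validation section says the outcome assessment phase has not been reached, so the change can still be specified in advance.

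The price is that the single overall interaction p-value no longer carries the claim; it can still be reported as a description of the pattern over time. If a plain T1-to-T3 change contrast were used instead of baseline adjustment, power would fall a few points below the overall test under the same assumptions (72% against 76% at rho 0.5; 92% against 95% at rho 0.7).

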## Abstract

Diabetic peripheral neuropathy (DPN) is the leading cause of disturbances in reactive balance control. The repeated, external mechanical perturbations in perturbation-based balance training(PBBT) evoke balance recovery strategies; which subsequently improve reactive balance performance. Using the practice schedule concept of motor learning in the design of PBBT is a relatively new approach related to balance exercises. This study aims to investigate the effects of blocked and random PBBT on reactive balance control and its persistency and transfer to conditions different from those experienced during training.

Individuals with DPN will be recruited and randomly allocated to one of the three groups: random, blocked, and control group. Random and blocked PBBT groups will receive single-session balance training, including unexpected perturbations of platform during quiet standing in two directions (anterior and posterior), and three difficulty levels of platform motion (displacement, velocity, and acceleration). Each balance perturbation in blocked group will be repeated over blocks of four trials. For the random group, perturbation sequence will be unpredictable for these four trials in each block. Primary outcomes (i.e., center of pressure variables, reaction time, movement time, and total response time variables) will be assessed at baseline as well as immediately and one day after intervention.

Specifications table

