### Interventions

For the intervention groups (random and blocked PBBT), the training will be performed by a different physical therapist. Patients in the control group will receive no intervention.

Participants will be stand on two force platforms of computerized dynamic posturography with one foot on each of the platforms. The intervention involves restoring body balance after unexpected perturbations through movement of the support base in the anteroposterior direction, for both directions at three levels of difficulty. Participants will be verbally instructed to maintain their body balance after support base displacements. Ground reaction forces underneath each leg will be recorded by two adjacently placed movable platforms of the computerized dynamic posturography device.

Participants will wear a safety harness supported by ropes tied at shoulder height, with the other end attached above their head. While these ropes will not limit balance recovery movements, they prevent participants from falling.

Researchers selected three difficulty levels for reactive balance training: low difficulty (3cm displacement amplitude; 5cm/s peak velocity and 70cm/s^2^ peak acceleration), medium difficulty (7/5cm displacement amplitude; 10cm/s peak velocity and 137cm/s^2^ peak acceleration), and high difficulty (15cm displacement amplitude; 15cm/s peak velocity and 260cm /s^2^ peak acceleration). From combining perturbation directions (anterior and posterior) and three difficulty levels of platform motion, six conditions of block perturbations will be generated.

In each block, participants will perform four trials for each perturbation condition, given by the combination of direction and difficulty levels, totaling 24 trials. In the blocked group, each balance perturbation will be repeated over blocks of four trials for participants. For the random group, the four perturbations of each block will be scheduled pseudorandomly and unpredictably, with no repetition of a perturbation condition (difficulty × direction) in consecutive trials.

The intervention groups will perform this single session PBBT after a five-minute rest at the end of the examining pre-intervention tests. The duration of each trial is 10 seconds and a 10 second rest is allowed between trials. In addition, a one-minute rest is given between blocks.

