### Sample size calculation

Due to a lack of similar studies, we conducted a pilot study on 30 individuals with diabetic neuropathy (10 for each group). Sample size was calculated in G*power software version 1.9.4.3 and was based on the primary outcome of the pilot study, the difference between means of the peak CoP velocity in the anterior direction measured with the computerized dynamic posturography at T1 and T2. Based on the statistical power of 80% and the probability of the first type error of 0.05, the sample size was estimated to be about 20 individuals in each group.

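### The aim is random versus blocked practice, but the analysis leaves that contrast as one of the Bonferroni post-hoc pairs behind a three-group test: valid, but needlessly weak for the trial's own question

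*Protocol article*

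**What the plan says.** All references are to the protocol article; no separate analysis plan is at hand.

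- **Aim.** The Background section says that "this study aims to compare the effects of blocked and random practice of PBBT on the acquisition, retention, and generalizability" of reactive balance skills. The protocol's name in the specifications table is also random versus blocked. The Abstract is looser: "This study aims to investigate the effects of blocked and random PBBT on reactive balance control", which could be read as each schedule against control.
- **Arms.** There are three. Under Interventions: "Patients in the control group will receive no intervention".
- **Analysis.** The Statistics section examines "The main effects and interactions of group (blocked sequence, random sequence, and control), time (pre-test and post-test" together with three difficulty levels, in a three-way repeated-measures ANOVA on the CoP variables. It repeats this for post-test against retention and adds further ANOVAs for transfer and for the stepping test. The last step is "A post-hoc Bonferroni test will be used for multiple comparisons". It does not say which family of comparisons this covers.
- **Sample size.** The sizing variable is peak anterior CoP velocity at T1 and T2. Power is set at 80% with a type I error of 0.05, and the section concludes that "the sample size was estimated to be about 20 individuals in each group". The section does not say between which groups the sizing difference lies, and gives no effect size or SD.

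**The concern.** Three arms give three pairs: random v blocked, random v control, blocked v control. Only the first answers the question in the Background section. The three-group test mixes all three, so it can be significant because training beats no training while the order of the perturbations makes no difference. The pair that does bear on schedule is treated like the two comparisons with control and pays for them through the Bonferroni adjustment.

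At stake is power. A trial with 20 patients per arm has little to spare, and a real difference between schedules could be missed only because the plan spreads its error rate over comparisons that are not its stated aim. There is also a risk at reporting: with no decisive contrast named, a significant group effect could be presented as the result on practice schedule.

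**Working it through.** **Inputs from the document:** 3 groups; about 20 per group (60 in total); type I error 0.05; power 80%; Bonferroni post hoc.

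**Assumptions:** two-sided tests; one standardised change score per patient, as a simplification of the repeated-measures ANOVA; equal SDs, with error pooled over three groups (df = 60 − 3 = 57); a Bonferroni family of exactly the three group pairs. The document gives no effect sizes, so a range is used.

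**Step 1. The plan's own sample size.** It cannot be reproduced, because effect size, SD, correlation, test family and contrast are not given. Solving backwards for 20 per group, 80% power and 0.05:
- as a two-sample t test, it implies a difference of d = 0.909 SD;
- as a three-group one-way F test with N = 60, it implies f = 0.411.

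Which of these, if either, was used is not known.

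**Step 2. What a significant three-group test can mean.** Let random = blocked exactly, both differing from control by t SD. The group means are then 0, t, t, so f = t√2/3 and the noncentrality is 60f². At t = 0.8: f = 0.377 and the noncentrality is 8.53. At t = 1.0: f = 0.471 and it is 13.33. Power of F with 2 and 57 df at 0.05, with no difference between schedules:

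| Trained minus control (SD) | Three-group test significant |
|---|---|
| 0.5 | 34% |
| 0.8 | 72% |
| 1.0 | 90% |
| 1.2 | 98% |

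**Step 3. Power for random versus blocked.** The noncentrality is d√(20/2). At d = 0.9 it is 0.9 × 3.162 = 2.846. The critical t with 57 df is 2.002 at 0.05 and 2.467 at 0.05/3 = 0.0167.

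| True random–blocked difference (SD) | Single contrast at 0.05 | One of three pairs at 0.0167 |
|---|---|---|
| 0.5 | 34% | 20% |
| 0.7 | 58.6% | 40.7% |
| 0.8 | 70% | 53% |
| 0.9 | 79.9% | 64.8% |
| 1.0 | 87.5% | 75.4% |

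The loss at 0.9 SD is 79.9 − 64.8 = 15.1 percentage points. At the implied d = 0.909, keeping 80% power at 0.0167 would need about 27 per group (3 × 27 = 81 patients instead of 60).

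**The case against.** The case for leaving the text alone has real weight.

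- **The plan does not stop at the three-group test.** It goes on to pairwise comparisons, and these will report random versus blocked. This stands: the plan nowhere claims that a significant group effect settles the question of schedule. Step 2 shows what that test cannot tell, not an error the authors have made.
- **Treating all pairs alike under Bonferroni is a legitimate, conservative choice,** and the Abstract's wording and the untreated arm fit an interest in all three pairs. It is valid. But the Background section and the protocol's name put one pair first, and the analysis does not.
- **A condensed article may leave the primary contrast to a fuller document.** That would answer a complaint about silence. Here the article does fix a route, ANOVA followed by undifferentiated Bonferroni pairs, and that route serves the aim poorly.
- **The size of the loss is conditional.** The effect sizes are assumed, the 0.0167 is derived rather than printed, and nothing says that 20 per group was sized for one pair at 0.05. This stands. The direction of the loss does not depend on it, and a wider Bonferroni family would make the loss larger.

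Two stronger readings are tempting and are not supported. A reader might infer that random versus blocked gets the least power of the three pairs. All three share the same group size, error term and threshold, so power is equal at equal effect, and the document gives no effects. A reader might also infer that Bonferroni is superfluous, since with three groups an overall F test followed by unadjusted pairs holds the family-wise error. That is true for one mean per group. This plan has interactions over three difficulty levels and several times. Simulating a null random–blocked pair tested unadjusted at each of three difficulty levels, with control far enough away that the overall test always rejects, gave at least one false positive in 11% to 14% of trials (assumed correlation 0.7 to 0).

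**Conclusion.** The point holds in a limited form. The planned route is valid but gives the trial's own question less power than it could have at no cost in patients. Under the assumptions listed, with 20 per arm, about 65% against 80% at a true difference of 0.9 SD, and 41% against 59% at 0.7 SD. A three-group result alone cannot support a conclusion on practice schedule.

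A reader might go further and infer that the analysis is wrong, or that it could yield opposite conclusions from the same data. The document supports neither. That training works and that the schedule matters are answers to different questions, and both can be true. This is an improvement the sponsor should make, not an error that invalidates the analysis.

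**What to change.** In Statistics:

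1. Name one primary contrast: random versus blocked on the change from pre-test to post-test (the group-by-time contrast, averaged over difficulty levels) in peak anterior CoP velocity, the variable used for sizing. Test it as a planned contrast at two-sided 0.05 and report it with its 95% CI.
2. Label random v control and blocked v control as secondary. Keep Bonferroni for these and for follow-ups by difficulty level or time.
3. State that no conclusion on practice schedule will be drawn from the three-group test alone.

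An overall F test followed by unadjusted pairs should not replace Bonferroni across the plan. If it is used at all, limit it to that single change score.

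The cost is a few sentences, with no added patients, visits or data. The downsides are that comparisons with control lose confirmatory standing, and that a pre-test to post-test contrast covers acquisition, so retention and transfer remain secondary. The Protocol validation section says that outcome assessment has not been reached, so the contrast can still be fixed before results are known.
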